### Outcomes, measures and follow-up assessments

2.7

Primary outcomes are cardiorespiratory fitness, functional capacity and HRQoL. Cardiorespiratory fitness will be assessed during a symptom-limited cardiopulmonary exercise test using an individualized gradual incremental ramp test designed to obtain oxygen consumption (VO_2_max). In brief, the VO_2_max test will consist of free-wheel pedaling with a cadence of 50–60 revolutions per minute (rpm) for 4 min on a cycle ergometer (Lode Corival, Groningen, The Netherlands), followed by 6 [New York Heart Association (NYHA) class II HF] or 10 (NYHA class III HF) watts increments every minute until the participant reaches volitional fatigue (i.e., cadence below 50 rpm or dyspnea over 8 on the Borg scale) or the emergence of test termination criteria (as extrasystoles, ST-segment elevation, arrhythmias or fibrillations on the electrocardiogram) (47). The maximal test criteria are: respiratory exchange ratio > 1.1, >85% of the age-predicted HRmax, <40 revolutions per minute, RPE >18, and plateau in VO_2_ (48). The gas exchange will be collected throughout the test using an indirect calorimeter/ergospirometer system (Cortex Metalyzer 3b (Cortex Medical, Leipzig, Germany), calibrated before the exercise test. Additionally, power output, ventilatory threshold, respiratory exchange ratio, oxygen pulse, ventilation, and respiratory rate will be assessed. HR will be recorded with a continuous telemetric HR sensor (Polar model H10, Finland) throughout the test and pos*t*-test. Additionally, if the criteria of the maximal test are not achieved, a time-limited test at 95% of the peak power output until fatigue is proposed as confirmation of the VO_2_ obtained (49). This individualized gradual incremental ramp protocol and the patient-limited nature of the test make the procedure feasible and safe even in patients with HF (12).

Functional capacity will be assessed by the six-minute walk test (6 MWT) following the American Thoracic Society Statement (50). Blood pressure, HR, oxygen saturation, and RPE will be evaluated before and immediately after the test. Patients will be instructed to walk as much as possible for 6 min. If the patients require it, breaks during the test will be allowed, but patients will be encouraged to resume walking as soon as possible. The total distance covered during the test will be recorded (meters).

HRQoL will be evaluated with the Minnesota Living with Heart Failure Questionnaire (MLHFQ) which is the most commonly used instrument for assessing HRQoL in HF patients. It contains 21 items assessing two dimensions: physical and emotional. The response options range from 0 (HRQoL unaffected) to 5 (maximum impact on HRQoL), with overall as well as dimension scores obtained from the sum of the respective items (51). This questionnaire has been validated in several languages, including Spanish (52). In addition, the generic questionnaire EQ-5D-5l will be applied, to support comparison with other health conditions and for future economic analysis of the intervention (53).

Secondary outcomes are:
–Program adherence and completion. For face-to-face activities, program adherence is defined as the percentage of total prescribed sessions completed. For home-based activities, the percentage of activities carried out at home of the prescribed ones will be computed, based on patient recordings in a diary. Program completion is considered as “yes” where participants attended most of the sessions and components of the CR intervention, and underwent a formal reassessment by the CR team at the end of the program (54).–Pro-B-type Natriuretic Peptide (BNP), as a biomarker with prognostic utility. When it is higher than 1,000 pg/ml, there is a higher probability of having events such as hospitalizations (55, 56). The determinations will be carried out in duplicate from serum samples by the fluorescence immunoassay technique in the laboratory of one of the participating centers (Hospital Clínico de la Universidad de Chile).–Functioning defined as the ability to perform basic, instrumental and advanced activities of daily living. It will be measured with the Activities of Daily Living Questionnaire—Technology (ADLQ-T). This instrument evaluates 7 areas related to self-care (6 items), home care and management (6 items), work and recreation (4 items), shopping and money (3 items), travel and transfers (3), communication (5 items) and technology (5). Each item is scored from 0 to 3, where 0 is no problem for the activity and 3 indicates that the activity cannot be performed. Additionally, when an aspect is part of the activities of the patient, it is scored 9. The ADLQ-T has been validated and proven useful in the Chilean population (57, 58).–Mortality and hospital admission will be measured separately and as a composite outcome. All-cause and HF-specific mortality and hospitalization will be differentiated. Death occurrence will be monitored by study personnel through a review of a public registry. The death certificate and any associated medical documentation will be copied for consideration by the adjudicating committee. Hospitalization occurrence will be assessed by study personnel through chart review at each participating center and supplemented by phone calls to participants every two months, using a standardized script. When the participant reports a hospitalization, all associated documents (i.e., tests and exam reports) will be collected from clinical charts at each center. A central adjudication committee will review all materials. This committee will be composed of three clinician-scientists (at least one will be a cardiology specialist) who will make the final decision about the event and specify the final death cause and hospitalization diagnosis with the corresponding ICD-10 code.–Upper and lower-body muscle strength will be assessed through grip strength and the chair stand test, respectively. Grip strength will be performed with a Jamar® Plus + electronic handheld dynamometer (Patterson Medical, Cedarburg, WI, USA) with the participant seated. Three attempts will be made on each hand alternately with 30 s of rest. The highest value of the 6 attempts will be reported (59). The chair stand test will be performed with the participant in a seated position in a chair without armrests and without wheels, feet flat on the floor, and arms crossed on the chest. From this position, they will be directed to rise fully and return to the starting position as many times as possible over 30 s. The number of repetitions achieved will be recorded (60).–Cost will be assessed through micro-costing from the perspective of health care system. A cost pool will be constructed for each CR program. The direct cost of labor (professional and administrative), depreciation of equipment and instruments, and the goods and services of normal consumption will be included. Indirect costs will also be considered, obtained from the calculation of indirect structural costs as an average percentage of direct costs in each center. Building depreciation costs will be discounted at a factor of 0.02, a rate obtained from a previous study performed by the Chilean Ministry of Health that included all public hospitals (61). In addition, out-of-pocket spending by patients will be costed (62), as too many patients are paying out-of-pocket for CR (63) and this impacts adherence.–Exercise-related adverse events: adverse events during exercise, such as myocardial ischemia or malignant arrhythmias, and serious adverse events, such as a death in the exercise sessions, will be reported to the corresponding ethics committee. All events will be registered for the final analysis.All outcomes will be measured at baseline, at 3 months (equivalent to stage three in the experimental group and at the end of the program in the control group), and at 12 months of follow-up from recruitment. The personnel assessing outcomes will be blinded to intervention assignment. In Table 4, all outcomes, their measurement, and assessment schedules are presented.

**Table 4 T4:** Outcomes, measures and assessment timing.

Outcome	Measure/source	Time point		
		Baseline	3rd month	1 year
Cardiorespiratory fitness	Symptom-limited cardiopulmonary exercise test with ergospirometer system	X	X	X
Functional capacity	6 min walk test	X	X	X
Health-related quality of life	Minnesota Living with Heart Failure Questionnaire and EuroQol-5 Dimensions.	X	X	X
Program adherence and completion	Attendance, checklist and diary.		X	
Pro-B-Type Natriuretic Peptide	Fluorescence immunoassay technique	X	X	X
Mortality and hospital admission (all-cause, cardiac-cause, and HF-cause)	Death certificate Clinical chart Medical documentation (labs, images, etc) Patient report	X	X	X
Skeletal muscle strength	Grip strength Chair stand test	X	X	X
Cost	Micro-costing method			X
Exercise-related adverse events	Checklist		X	

HF, heart failure.

In addition, sociodemographic and clinical data will be collected to compare the groups at baseline and other measures of functionality, diet, self-efficacy and perceived social support will be collected as input for the individualization of interventions.

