**Methods and analysis:**

A 2 parallel-arm, multi-center randomized clinical superiority trial will be conducted with blinded outcome assessment. 152 HF patients (NYHA class II or III) will be recruited consecutively, and randomly assigned using permuted blocks; allocation will be concealed. The 12-week intervention will include evaluation, medical and nurse management, aerobic interval training, resistance exercise training, psychosocial support, and education. These will initially be delivered in a center, transitioning to home in 4 stages. Controls will receive similar management, but face-to-face continuous aerobic exercise sessions and resistance exercises. The main outcomes are cardiorespiratory fitness (VO_2_ max), functional capacity (m from 6 MWT), and quality of life (Minnesota Living with Heart Failure Questionnaire). Program adherence and completion, NT-proBNP, functioning, all-cause and HF-specific mortality and hospitalization, muscle strength, adverse events and cost will be secondary outcomes. These will be measured at baseline, end of intervention, and 12-month follow-up. The sample size was calculated considering 90% power, a significance level of 5%, a between-group difference equivalent to 1/2 MET, and a 10% potential loss to follow-up. Intention-to-treat analysis will be considered. Between-group differences will be assessed using Student's *t*-tests or *Z*-tests along with 95% confidence intervals, and the rate ratio will be computed to compare mortality.

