### Sample size

2.3

One hundred and thirty-eight patients (69 per group) are required to have a 90% chance of detecting as significant at the 5% level, a difference in the primary outcome measure of maximum cardiorespiratory capacity (VO_2_ max), assuming 15 ml/Kg/min in the control group and 16.75 ml/Kg/min in the experimental group at intervention end. The VO_2_ max assumed in the control group is that achieved by the experimental group with exercise-based CR in the HF-ACTION trial (9), with a standard deviation of 3.15 calculated with the range rule. The VO_2_ max in the experimental group was assumed with an intermediate minimal important difference of 1/2 MET (1.75 ml/kg/min) (30, 31). If a potential 10% loss of follow-up is added, results in 152 patients (76 per group). Sample sizes were also calculated for the other two primary outcomes, functional capacity, and HRQoL, with fewer patients needed to test the underlying hypothesis.

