### Analysis plan

2.8

Baseline characteristics will be compared among the two arms of the study. This would ensure the identification of any chance imbalances despite randomization. Intention-to-treat analysis will be considered. At each follow-up point, a comparison between groups will be made. Student's *t*-tests will be used to compare the means for continuous variables (upon checking of assumptions), and confidence intervals for mean differences will be provided. For dichotomous outcomes (other than mortality), the *Z*-test for comparison of proportions will be computed along with 95% confidence intervals for the difference of proportions. To compare mortality between groups, the mortality rate ratio will be computed with 95% confidence intervals.

In case of imbalances in baseline characteristics, a multiple linear regression model will be fitted for continuous outcomes, multiple logistic regression for dichotomous outcomes, and Poisson regression (or Negative binomial) for mortality.

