## Discussion

3

In response to knowledge gaps and emerging evidence regarding alternative exercise interventions and delivery models for comprehensive CR in HF, we propose the CO-CREATION-HF trial. We hypothesize that a 6-month comprehensive and hybrid model of CR, with interval exercise and self-efficacy/motivation promotion as underpinnings, will improve adherence and completion of CR, resulting in improved cardiorespiratory fitness, functional capacity, and QoL. In addition, hybrid delivery –with a 4-step transition from a typical supervised program to a patient self-administered program- may lead to lower costs for both the health system and the patient. In our model, exercise will be prescribed at the volume and intensities necessary to achieve the expected physiological effects in HF patients and patients will be supported to adhere to it.

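### Three outcomes are called primary and compared at two visits with no rule for success, while the stated 5% level and 90% power belong to a single test of VO2max at the end of the intervention

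*Protocol article*

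**What the plan says.** The Outcomes section states: "Primary outcomes are cardiorespiratory fitness, functional capacity and HRQoL". The abstract gives the same three, unranked: "The main outcomes are cardiorespiratory fitness (VO_2_ max), functional capacity (m from 6 MWT), and quality of life (Minnesota Living with Heart Failure Questionnaire". The Discussion also keeps functional capacity and HRQoL as primary.

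The visit schedule begins "All outcomes will be measured at baseline, at 3 months" and adds a 12-month visit. The Analysis plan says: "At each follow-up point, a comparison between groups will be made". Continuous outcomes are compared by Student's t-test with confidence intervals. The article states no adjustment and no order of testing.

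The Sample size section attaches the 5% level and 90% power to VO2max only, "assuming 15 ml/Kg/min in the control group and 16.75 ml/Kg/min in the experimental group at intervention end", with a standard deviation of 3.15. Of the other two it says: "Sample sizes were also calculated for the other two primary outcomes, functional capacity, and HRQoL, with fewer patients needed to test the underlying hypothesis". It gives no figures for them.

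The Discussion says that the model will be available for implementation if superiority is shown, but does not say which result would show it. It does call maximum exercise capacity the basis of the hypothesis.

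**The concern.** A trial with several primary outcomes needs a rule linking them to its conclusion: any one, all, or a fixed order. The rule decides which error rate and which power apply. Here the article fixes three primaries, two comparison times and a sample size, and the sample size corresponds to one of the six comparisons.

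The results are meant to support adoption in a health system. Without a rule, a single favourable result among six could be presented as superiority, and the headline comparison could be picked after the data are seen. In that case neither the 5% nor the 90% would describe the conclusion being drawn.

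**Working it through.** **Inputs from the article.** Three primary outcomes; two follow-up visits; 3 × 2 = 6 comparisons. For VO2max: difference 16.75 − 15 = 1.75 ml/kg/min, SD 3.15, level 5%, power 90%, allocation 1:1, loss 10%.

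**Assumptions.** The article gives no correlations between outcomes or between visits, so ranges are shown. A 5% level for each outcome is inferred from the single stated level and the 95% intervals. Sidedness is not stated. Two-sided reproduces the stated size, whereas one-sided would give 56 per arm.

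**1. Reproduce the stated size.** n per arm = 2(1.960 + 1.282)² × 3.15² / 1.75² = 68.1, rounded up to 69, or 138 in total, as stated. Power at 69 per arm is 90.4% (normal approximation) or 90.0% (noncentral t). Adding 10%: 69 × 1.10 = 75.9, so 76 per arm and 152 in total, as stated. The figures are right for one test of one outcome at one visit.

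**2. Rule: any one primary result at unadjusted 5%.** If the tests are independent:
- three outcomes at 3 months: 1 − 0.95³ = 14.3%
- six tests: 1 − 0.95⁶ = 26.5%

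With correlated test statistics (multivariate normal simulation, 1,000,000 draws, |z| > 1.96; in the six-test column the between-visit correlation is 0.6):

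| Between-outcome correlation | Three tests at 3 months | Six tests |
|---|---|---|
| 0 | 14.3% | 24.1% |
| 0.3 | 13.6% | 23.0% |
| 0.5 | 12.6% | 21.2% |
| 0.8 | 9.9% | 16.7% |

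These are two-sided rates.

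**3. Rule: alpha split equally over three outcomes at one visit.** Alpha = 0.05/3 = 0.0167. VO2max power at 69 per arm falls to 80.8% (normal) or 79.8% (noncentral t). Restoring 90% needs 2(2.394 + 1.282)² × 3.15² / 1.75² = 87.5, so 88 per arm.

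**4. Rule: all three must succeed at one visit.** The error stays at or below 5%. If each outcome had exactly 90% power, joint power would be 0.9³ = 72.9% under independence and 82.7% at correlation 0.8. The article says that the other two need fewer patients, so on its own assumptions their power at 69 per arm exceeds 90%, which makes 73% a lower bound. If each of them had an assumed 95%, joint power would be 81% to 84% for correlations 0 to 0.5. It cannot exceed VO2max's own 90%.

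**5. Rule: fixed sequence starting with VO2max at 3 months.** The first test uses the full 5%, so its power is 90% at 69 per arm. Each later test is reached only after a significant result, so the overall error stays at 5%. Both stated figures hold for the VO2max test.

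**The case against.** The strongest reply is that the article does signal a lead outcome. The Sample size section refers to VO2max in the singular as the primary measure, the abstract's calculation uses only the half-MET difference, and the Discussion rests the hypothesis on exercise capacity. That is fair, and it makes the repair easy. It is not a testing order, however, because the same sections still call the other two primary.

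A second reply is that a multiplicity rule may sit in an analysis plan that is not shown. It may, and its absence alone would be no finding. But the article already fixes three primaries, comparisons at both visits and a size for one unadjusted test. An alpha split adopted later would lower VO2max power below 90%, and an all-three rule would generally leave joint power below 90%. Only a rule that gives VO2max at 3 months the full 5% first keeps both figures.

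The remark that the other outcomes need fewer patients concerns the power of each outcome on its own. It does not control error across them.

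Three stronger readings are not supported:
- **The 5% and 90% require VO2max to be the only primary outcome.** They do not: step 5 keeps both with three primaries.
- **The time point used for sizing is undefined.** The abstract schedules outcomes at baseline, end of intervention and 12 months, and Table 4 gives the same three visits as baseline, 3 months and 1 year. Intervention end is therefore the 3-month visit.
- **The article declares that any single result would count as success.** It does not; it leaves the matter open.

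**Conclusion.** The point holds. The design arithmetic is correct for one test of VO2max at 3 months, but the article presents three primaries at two visits and does not say how they lead to a conclusion.

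The size depends on the rule eventually used. Under an any-one rule, the false-positive risk is about 10% to 14% for three tests, and about 17% to 24% for six (26.5% if all six were independent). Under an equal split over three, VO2max power is about 80%. Under an all-three rule, the 5% is kept and joint power lies between about 73% and 90%, depending on the unstated power of the other two outcomes. All the correlated figures rest on assumed non-negative correlations.

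The rule should be settled before any comparative data are seen, since that is what prevents selection of the headline result.

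**What to change.** State that superiority is judged on VO2max at 3 months, two-sided 5%. Then test 6MWT distance and MLHFQ total score at 3 months in a pre-specified fixed sequence, each at two-sided 5% and only if the preceding test is significant. The investigators choose the order of these two, and both may keep the label primary within the hierarchy. Label all 12-month comparisons secondary. In the Sample size section, replace the reference to intervention end with 3 months, as the abstract and the visit schedule already imply.

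The cost is wording in the protocol, and in the analysis plan if one exists. The sample size stays at 152. The downside is that 6MWT or MLHFQ cannot be claimed as confirmatory if an earlier test in the sequence fails.

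Separately, reconcile the descriptions of the experimental programme's length. The abstract has "The 12-week intervention will include evaluation", the Discussion has "We hypothesize that a 6-month comprehensive and hybrid model of CR", and Table 3 runs stage 4 to week 24. This does not change which visit was used for sizing.

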3. Home-based with monitoring	– Training is carried out at home and is monitored through a call at least once a week by the physiotherapist. – Psychosocial support and adherence to exercise, diet and medication will be promoted through phone calls once a week. – If necessary, a face-to-face session would be offered at this stage to reinforce any identified challenges and for progress evaluation.	– This stage will last 4 weeks or more, through to 12 weeks.
4. Home-based without monitoring	– The patient will do the training at home unsupervised. – Phone calls will be held once every two weeks for two months, and then once a month through to the 6 months. – These calls will be designed to reinforce adherence and resolve patient questions regarding exercise, diet, or medication.	– From week 12 to week 24.

The comprehensive, hybrid CR program will begin with an initial evaluation that includes all necessary assessments to prescribe exercise training as well as dietary and adherence promotion interventions (Table 3, Figure 3). The exercise component includes aerobic interval training and resistance exercises. The center-based training will be performed on an ergometer bike; as the CR program progresses, the training will be adapted to a modality that can be undertaken by the patient at home, such as using of a footstool, static bike if it is available, or walking outdoors.

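### Table 4, the text of section 2.7 and the stated programme length disagree on whether exercise-related events and adherence are recorded in weeks 12 to 24

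*Protocol article*

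**What the plan says.** **Schedule in Table 4.** The columns are baseline, 3rd month and 1 year. The row "Exercise-related adverse events" (source: a checklist) has one mark, under 3rd month. So does the row for adherence and completion, whose source is "Attendance, checklist and diary".

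**Schedule in the text of section 2.7.** "All outcomes will be measured at baseline, at 3 months (equivalent to stage three in the experimental group" and the end of the control programme), and again at 12 months from recruitment. On adverse events the text adds "All events will be registered for the final analysis", with no time window. The same section sends the reader to Table 4 for the assessment schedule.

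**Programme length.** The abstract has "The 12-week intervention will include evaluation, medical and nurse management". In Table 3, stage 4 of the experimental programme runs from week 12 to week 24, and "The patient will do the training at home unsupervised". The Discussion has "We hypothesize that a 6-month comprehensive and hybrid model of CR". Section 2.6 gives the control programme 10 to 12 weeks and 20 supervised sessions.

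**Other follow-up after month 3.** Section 2.7 follows deaths through a public registry. It follows admissions through chart review and scripted calls to participants every two months, with central adjudication. Table 3 also provides stage-4 calls in the experimental arm, described as reinforcing adherence and answering questions.

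**The concern.** The model under test moves patients from supervised to unsupervised exercise. Its safety and uptake are least certain once supervision and weekly monitoring have stopped, which is stage 4. If Table 4 is followed as printed, the only scheduled reading of exercise-related events and of adherence comes before that stage begins.

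Two things are at stake:

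- **Safety.** An event during home exercise that leads to neither admission nor death would have no scheduled route into the data in weeks 12 to 24. A report could then describe exercise safety for the whole model from its more closely supported half.
- **Adherence.** The Discussion ties better adherence and completion to a 6-month model, while the schedule supplies data for about half of it. Completion also requires a formal reassessment at programme end (section 2.7). If the programme ends at week 24, no assessment is scheduled there.

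Events and diary entries that were not collected cannot be recovered by an analysis plan written later.

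**Working it through.** The plan gives no figure for the share of home exercise covered by its assessments, so there is nothing to reproduce. The check is a comparison of the passages and a count.

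**1. The passages side by side**

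| Place | Adverse events and adherence | Programme length |
|---|---|---|
| Abstract | baseline, end of intervention, 12 months | 12 weeks |
| Table 3 | not addressed | to week 24 |
| Section 2.7, text | baseline, 3 and 12 months; all events registered | month 3 is stage three for the experimental arm, programme end for controls |
| Table 4 | month 3 only | not addressed |
| Discussion | not addressed | 6 months |

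Neither schedule can be taken literally throughout. Programme adherence cannot be measured at baseline, so the general sentence in section 2.7 is too broad. Table 4 has no row for functioning, a secondary outcome in the same section, so the table is not complete. The abstract also fits all four stages into its 12 weeks, whereas Table 3 places stage 4 after week 12.

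**2. Inputs for the count** (month 3 taken as week 12; nominal stage lengths)

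- Stage 2, partly home-based: weeks 4 to 8, so 4 weeks (Table 3).
- Stage 3, home-based: weeks 8 to 12, so 4 weeks (Table 3).
- Stage 4, home-based: weeks 12 to 24, so 12 weeks (Table 3).
- Interval training 3 times a week; resistance training at least twice a week (section 2.5).
- Assumptions: these frequencies continue in stage 4. Stage-2 resistance work is done at home. Stage-2 home interval sessions are not stated, so 0, 1 and 2 a week are tried.

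**3. Share of home exercise after month 3, by weeks** = 12 / (home weeks before month 3 + 12)

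- Fully home-based weeks only: 12 / (4 + 12) = 75%.
- All of stage 2 counted as home weeks: 12 / (4 + 4 + 12) = 60%.
- Stage 1 ending as early as week 1 (Table 3 allows an early end), so stage 2 lasts 7 weeks: 12 / (7 + 4 + 12) = 52%.

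**4. By sessions** (3 interval + 2 resistance a week)

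- Stage 4: 12 × 5 = 60. Stage 3: 4 × 5 = 20. Stage 2: 4 × 2 = 8 resistance, plus 4*h* interval, where *h* is the weekly number done at home.
- Share = 60 / (88 + 4*h*): 68% for *h* = 0, 65% for *h* = 1, 63% for *h* = 2.

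**5. Share of the programme**

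- 12 / 24 = 50% of the weeks in Table 3, and all 12 weeks of stage 4.

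**6. Could existing contacts fill the gap?** If the two-monthly calls are counted from recruitment, those at months 4 and 6 would cover stage 4, and they go to participants in both arms. Their stated purpose is admissions. The stage-4 calls exist in the experimental arm only, so relying on them would make ascertainment unequal.

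**The case against.** The strongest answer is that the text, not the table, states the intention: all events registered, all outcomes measured again at 12 months. Deaths and admissions are followed throughout, so an arrhythmia or ischaemic event that brings a patient into hospital would be found, though not labelled as exercise-related. The call scripts and the adverse-event checklist are not shown, and an article commonly leaves these to the full protocol.

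Much of this stands. A reader might infer from Table 4 that no safety information is collected after month 3. The document does not support that. What remains is narrower: events causing neither admission nor death, on the Table 4 schedule. The text does not close this gap, because it gives no window or source for registering events, refers to Table 4 for timing, and otherwise offers only an assessment nine months later. Its own serious example, "serious adverse events, such as a death in the exercise sessions, will be reported to the corresponding ethics committee", is tied to exercise sessions and does not say how events at home come to notice.

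On adherence the objection is stronger. The control programme ends at 10 to 12 weeks, so month 3 is the only window in which both arms have a prescribed programme. A reader might conclude that the adherence hypothesis cannot be tested. That follows only if the 6-month wording defines the programme; for the first 12 weeks, month 3 is the right time for a between-arm test. Stage 4 is labelled as being without monitoring, so leaving adherence unmeasured there may be deliberate.

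**Conclusion.** The point holds as a contradiction that needs settling, with a real gap on one of its readings. Table 4, the text of section 2.7 and the programme length cannot all be right. If Table 4 is followed, all 12 stage-4 weeks have no scheduled capture of exercise-related events short of admission or death, and no adherence data. That is half of the 24-week programme and about 52% to 75% of home exercise.

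The range rests on nominal stage lengths, month 3 taken as week 12, and unchanged training frequency in stage 4. Every variant exceeds half, but 75% is the top of the range and should not be quoted alone. A reader might also multiply 36 stage-4 interval sessions (3 × 12) by 76 patients to get 2,736 uncovered sessions. That is a ceiling, since it needs full adherence and no losses, while the plan itself allows for 10% loss.

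Both outcomes are secondary. The primary outcomes are assessed at 3 and 12 months in any case, and the sample size is based on VO2 max, so neither is affected.

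**What to change.** 1. **Reconcile the documents.** Use one programme length in the abstract, Table 3 and the Discussion, and make Table 4 agree with section 2.7. Which length applies is for the sponsor to settle. Cost: wording.
2. **Adverse events.** Extend the Table 4 row to cover weeks 12 to 24 and state the collection window for each arm. Add the same exercise-event items to the standardised two-monthly calls in both arms, so that ascertainment is equal. Cost: a few questions in calls already planned, with no extra visit.
3. **Between-arm adherence.** Keep this comparison at month 3, the window common to both arms. Report observed attendance and diary-based home adherence separately, because control sessions are supervised while home sessions are self-recorded. Cost: none in data collection.
4. **Stage-4 adherence.** Either describe it in the experimental arm only, or limit the adherence hypothesis to the first 12 weeks. The first option has a small cost: diaries continued and retrieved, or adherence recorded during the stage-4 calls, since no visit falls between months 3 and 12. The second costs only wording. If the programme is defined as running to week 24, also say when the reassessment needed for completion takes place.
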